## Abstract

**Introduction:**

Poor diet is a leading risk factor for non-communicable diseases and costs the National Health Service £5.8 billion annually. Product placement strategies used extensively in food outlets, like supermarkets, can influence customers’ preferences. Policy-makers, including the UK Government, are considering legislation to ensure placement strategies promote healthier food purchasing and dietary habits. High-quality scientific evidence is needed to inform future policy action. This study will assess whether healthier placement strategies in supermarkets improve household purchasing patterns and the diets of more than one household member.

**Methods and analyses:**

This natural experiment, with a prospective matched controlled cluster design, is set in discount supermarkets across England. The primary objective is to investigate whether enhanced placement of fresh fruit and vegetables improves household-level purchasing of these products after 6 months. Secondary objectives will examine: (1) differences in intervention effects on purchasing by level of educational attainment, (2) intervention effects on the dietary quality of women and their young children, (3) intervention effects on store-level sales of fruit and vegetables and (4) cost-effectiveness of the intervention from individual, retailer and societal perspectives. Up to 810 intervention and 810 control participants will be recruited from 18 intervention and 18 matched control stores. Eligible participants will be women aged 18–45 years, who hold a loyalty card and shop in a study store. Each control store will be matched to an intervention store on: (1) sales profile, (2) neighbourhood deprivation and (3) customer profile. A detailed process evaluation will assess intervention implementation, mechanisms of impact and, social and environmental contexts.

**Ethics and dissemination:**

Ethical approval was obtained from the University of Southampton, Faculty of Medicine Ethics Committee (ID 20986.A5). Primary, secondary and process evaluation results will be submitted for publication in peer-reviewed scientific journals and shared with policy-makers.

**Trial registration number:**

NCT03573973; Pre-results.

Strengths and limitations of this studyThis study is unique; unlike current literature, it will provide evidence of product placement intervention effects from a cluster trial with adequate statistical power.The outcomes of this study include household purchasing data from loyalty card use over a 9-month period, as well as dietary quality derived from food frequency questionnaires administered at four different time points.This is the first supermarket placement study to provide dietary quality outcome data from more than one household member.Randomisation of stores was not possible within this commercial setting, however, the criteria used to match stores increases the similarity of intervention and control stores and reduces effects of confounding.This study tests a single component intervention; this is scientifically advantageous because it enables assessment of the isolated effects of this particular placement intervention, which improves the availability of fresh fruit and vegetables and positions them in the prominent front-of-store location.

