### Study setting

WRAPPED focuses on women from disadvantaged backgrounds and will, therefore, sample from customer who shop at stores of the collaborating discount supermarket chain situated in more socioeconomically deprived neighbourhoods across England. The collaborating supermarket has over 900 stores nationwide and holds approximately 2% of the grocery market share in the UK.^23^

This study will sample 36 stores, 18 intervention and 18 control stores; allocation to intervention condition will be at the store level. Intervention stores will be selected, in a phased approach, from the collaborating supermarket’s ongoing refurbishment programme. Randomised controlled trial methodology in real-world supermarket research is limited because it requires commitment that is problematic in this highly competitive, commercial setting. In WRAPPED, randomisation of stores is also not viable within the company’s business model. Consequently, control stores will be matched to an intervention store based on: (1) sales profile, (2) customer profile and (3) neighbourhood deprivation (Index of Multiple Deprivation).^24^Matching on these factors increases the similarity of intervention and control stores and reduces effects of confounding. We will seek to select control stores located at least 20 miles from an intervention store to reduce contamination effects of control women shopping at intervention stores.

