### Intervention and control conditions

The WRAPPED intervention incorporates both placement interventions from the typology of interventions in proximal physical micro-environments: availability and position.^25^ The intervention creates a healthier store layout by expanding the produce section to increase the availability of fresh fruit and vegetables, and positioning the section towards the front of the store. The supermarket chain will implement the intervention and will cover new display infrastructure and staff training costs (quality management, etc). The intervention will be implemented throughout the year, excluding the Christmas retail period, phased across 22 months and commencing in 2019. The logic model (figure 2) specifies the intervention components and the route of impact for the short term, medium term and long term. The model specifies that disadvantaged women will be exposed to the in-store product placement changes which will increase their purchasing of fresh fruit and vegetables (short-term outcome) that in turn will improve their own and their young children’s dietary quality (medium-term outcomes) and subsequently reduce inequalities in diet and obesity (long-term outcomes). This study will assess the short-term and medium-term outcomes.

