**Figure 2 F2:**
[figure not shown]
Logic model for the Women’s Responses to Adjusted Product Placement and its Effects on Diet study. PPI, patient and public involvement. F&V, fruit and vegetables.

The control condition is the previous layout of stores with a limited range of fresh fruit and vegetables, placed at the back of the store. Both control and intervention stores will be sampled from locations across England to improve generalisability.

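### The two-arm contrast estimates wider range plus front-of-store position delivered within a store refurbishment; it cannot give the isolated effect of placement that the article claims

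*Protocol article*

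**What the plan says.** The strengths and limitations list after the abstract states: "This study tests a single component intervention; this is scientifically advantageous because it enables assessment of the isolated effects of this particular placement intervention". The sentence goes on to define that intervention as one "which improves the availability of fresh fruit and vegetables and positions them in the prominent front-of-store location".

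The section on intervention and control conditions says: "The WRAPPED intervention incorporates both placement interventions from the typology of interventions in proximal physical micro-environments: availability and position". In the store this means "expanding the produce section to increase the availability of fresh fruit and vegetables, and positioning the section towards the front of the store". The chain also pays for new display infrastructure and staff training.

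On the source of stores, the study setting section says: "Intervention stores will be selected, in a phased approach, from the collaborating supermarket’s ongoing refurbishment programme". Allocation is not randomised, and there are two arms of 18 stores. For the comparator: "The control condition is the previous layout of stores with a limited range of fresh fruit and vegetables, placed at the back" of the store.

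The primary outcome section sets baseline as the three months before refurbishment and the main follow-up as months 3 to 6 after it. Store sales use the same time origin. The economic evaluation section takes the refurbishment programme as the thing whose costs and effects are estimated.

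**The concern.** A claim to isolate an effect needs a comparison in which only that feature differs between arms from time zero. Here the placement change arrives as part of a refurbishment, in one arm only, and time zero is the refurbishment. If a refurbished store draws more visits or larger baskets, part of any rise in produce purchasing would occur without any change in range or position.

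The audience makes this matter. The abstract and introduction set the study against possible placement legislation, and the dissemination section promises policy briefings. A rule about where produce is placed would not bring a refurbishment with it. Calling the result an isolated placement effect would tell policy-makers something that the comparison does not show.

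**Working it through.** The claim rests on no figure, so the check is mainly a comparison of statements.

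1. **What differs between arms after time zero.**
   - Intervention: larger produce section, front position, new display infrastructure, staff training, and any other element of the refurbishment (intervention and control conditions; study setting).
   - Control: previous layout, limited range, back of store.
   - That control stores are not refurbished is an inference from these two descriptions; the article does not use the word.

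2. **What the design can identify.** Write the expected between-arm difference in change as D = R + P + I + G. R is the effect of range, P of position, I their joint action, and G any general refurbishment effect on produce purchasing. Two arms yield one contrast, D, and four unknowns. No arm has range only, position only or refurbishment only. R + P + I equals D only if G = 0, and nothing in the article establishes that.

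3. **Whether existing safeguards remove G.**
   - Matching on sales profile, customer profile and deprivation, and adjustment for baseline purchasing, deal with differences present before time zero. G starts at time zero in one arm.
   - The frozen fruit and vegetable analysis is stated to be for substitution.
   - Changes in product-group sales appear in the economic evaluation as possible inputs to the retailer's costs.
   - The in-store surveys in the process evaluation can record what else changed. They cannot estimate its effect.

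4. **How large G would have to be to matter.** Baseline purchasing is not given. If the baseline mean is b items per week and everything bought rises by a proportion g, then G = b × g. It equals the target difference of 0.3 items (sample size section) when g = 0.3/b. With assumed baselines:
   - b = 1: 0.3/1 = 30%
   - b = 1.5: 0.3/1.5 = 20%
   - b = 2: 0.3/2 = 15%
   - b = 3: 0.3/3 = 10%

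   The baseline could be lower. The stated SD is 0.7, so the variance is 0.7² = 0.49. If that SD describes single weekly counts, the negative binomial model under consideration would imply a mean below 0.49 and g above 0.3/0.49 = 61%. If the SD describes averaged data, this bound does not apply. These figures show what would be needed; they are not evidence that any uplift occurs.

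5. **What a share analysis can show.** Let T be total items. Under a uniform uplift the produce share goes from b/T to b(1+g)/(T(1+g)) = b/T, so it does not move. A rise in share is therefore evidence of a produce-specific change. If better produce also leads women to buy more of other things, the share understates the placement effect. If produce displaces other items, the share rises further and the fall in other items can hide a general uplift.

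6. **Side check on power.** Design effect 1 + 29 × 0.1 = 3.9. Effective n per arm = 16 × 30/3.9 = 123.1. With a difference of 0.3 and SD 0.7, power is 92.0% by the normal approximation and 90.2% with a t distribution on 30 degrees of freedom. The stated 90% stands, and this point does not touch it.

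**The case against.** The strongest reply is that the sentence defines its own terms. It goes on to name availability and position together, and the primary objective tests them jointly. Single component can then mean placement alone, without pricing or information. This stands. A reader might infer that the article claims to tell range from position, or that the component count is a plain contradiction; read in full, the sentence does not support that. This reading does not rescue the word isolated, because the refurbishment remains in the contrast.

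Second, nothing in the article says that the refurbishment changes more than the produce section. Display infrastructure and training are presented as costs of the intervention, and some sections call the same time point intervention commencement. This also stands, and it limits the point: a general effect is possible but not shown.

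Third, a negative-control model is something an analysis plan might contain, and that plan is not at hand. So one can say only that this article states no such analysis, not that none is planned. The interpretive claim is too strong either way.

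Fourth, a rule crediting placement only when produce rises beyond control categories would be unsound. The economic evaluation itself anticipates complements and displacement, so other categories may respond to placement. This is accepted.

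**Conclusion.** The point holds for the word isolated and for what the trial can conclude. The design estimates the combined effect of expanded range and front-of-store position delivered within a store refurbishment. It separates neither range from position nor either of them from a general refurbishment effect. The size of any general effect is unknown, and the percentages above depend on baseline means that the article does not give.

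A reader might go further and infer that a positive result would be mostly refurbishment uplift. The article does not support that: it does not list what else changes and gives no data on overall purchasing. The conclusion rests on one inference, that control stores are not refurbished during follow-up. The comparison, primary outcome and sample size are not called into question.

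**What to change.** - **Wording.** In the strengths and limitations list, replace the reference to isolated effects with *combined effect of expanded range and front-of-store position delivered within a store refurbishment*. State as a limitation that these elements cannot be separated. Carry the same wording into results and policy briefings.
- **Supportive analysis, prespecified.** Run the primary model on total non-produce items, or on categories that the in-store surveys confirm were not moved. Analyse fresh fruit and vegetables as a share of all items as well. The share is undefined in weeks with no purchases, so compute it per woman over each three-month period. The primary outcome section describes item counts for each product at each visit; the fix assumes that these cover all products.
- **Use.** Report these results beside the primary result to inform interpretation. They should not decide attribution on their own, because complements and displacement can move other categories. They also cannot split range from position, so the wording change is needed in any case.

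The cost is one or two extra models on data already requested, and a less favourable claim.

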## Introduction

Poor diet is a leading risk factor for obesity and non-communicable diseases.^1^ In the UK, the cost of poor diet-related ill health to the National Health Service (NHS) is £5.8 billion annually, and as many as 42 000 deaths could be prevented each year if people ate more fruit and vegetables.^2^ Inadequate intake of fruit and vegetables is of particular concern among low-income groups.^3^

Women represent an important target group for improving the diets of the broader population; they remain household food gatekeepers, dominating decisions about food shopping,^4^ plus the short-term and long-term health of children is influenced by their mothers’ food choices.^5^ The Scientific Advisory Committee on Nutrition has expressed concern over the poor diets of young women in the UK and the impact on their children.^6^ Improving the nutritional status of women before, during and after pregnancy is important for obesity prevention and is a priority in UK policy (Healthy Lives Healthy People; The Health of the 51%: Women).^7 8^ Identifying strategies that support women of childbearing age, particularly those from disadvantaged backgrounds, to make healthy food choices could improve public health now and in the future.

Systematic reviews have shown that interventions providing information about healthy dietary behaviours alone are largely ineffective among disadvantaged groups and that campaigns such as ‘5-a-day’ may even increase inequalities.^9 10^ Evidence for interventions that are effective among disadvantaged populations remains limited, however, those addressing the broader environmental determinants of diet appear most promising.^11^ It has been purported that information campaigns may be amplifying inequalities because they require high psychological agency, or conscious awareness of behavioural habits, which tends to be lower among disadvantaged groups.^12^ In contrast, alterations to environmental stimuli can evoke unconscious reactions or improvements in health behaviours.^13^ UK observational research supports this notion and suggests that unhealthy food environments may be exacerbating dietary inequalities. In Cambridgeshire, associations between exposure to fast food outlets and fast food intake were most pronounced among adults of low socioeconomic status.^14^ In Hampshire, shopping at less healthy supermarkets, with poorer availability, pricing and placement of healthy foods, was associated with poor dietary quality among women who left school aged 16 years but not among those with degree qualifications.^15^

Almost 90% of UK grocery sales occur within supermarkets^16^ and the subtle use of marketing techniques influences the food choices of an almost captive market. A recent survey suggests that two-thirds of all placement marketing strategies used to promote food and beverages in UK supermarkets were for unhealthy products.^17^ Additionally, discount and small supermarkets have been shown to have less healthy in-store environments than other supermarkets, including poorer placement of fresh fruit and vegetables.^18^ This is concerning because these types of stores are used more regularly by disadvantaged families and younger adults who have poorer dietary behaviours.^15 19^ The UK government is considering banning the prominent placement of unhealthy foods in outlets like supermarkets.^20^ Evaluating strategies in discount or small supermarkets that aim to improve the placement of fruit and vegetables could expand the government’s intended policy and would aid understanding of their effects among a population with the most to gain from dietary improvements.

Systematic reviews of supermarket interventions targeting the in-store environment, such as product placement strategies that alter the availability and positioning of healthy or unhealthy foods, show promising effects.^21 22^ The majority of studies, however, have poor methodological quality. Many have not included a control group nor reported sample size calculations, and none included an adequate number of stores for a cluster design study. Additionally, very few studies assessed the effect of product placement changes on outcomes at the individual level (ie, customers’ purchasing and dietary patterns), with most assessing change at the store level ([name], [name], [name], [name], unpublished). Not a single study reported on cost-effectiveness.^22^ Further high-quality, adequately powered studies are needed to quantify the effect of placement interventions in supermarkets. Studies that measure cost-effectiveness and examine differential effects by socioeconomic status are particularly important for policy-makers. The collaboration with a discount supermarket chain established for this study provides a unique opportunity to evaluate, on a large scale, the effectiveness and cost-effectiveness of creating a healthier store layout in supermarkets frequently used by disadvantaged families.

## Study objectives

### Primary objective

To assess whether increasing the availability of fresh fruit and vegetables and positioning them at the front of the store in discount supermarkets improves fresh fruit and vegetable purchasing patterns 6 months after intervention commencement among women customers aged 18–45 compared with control customers.

### Secondary objectives

To assess effect modification by educational attainment on women’s change in fruit and vegetable purchasing.To assess how the intervention affects women’s dietary quality and daily fruit and vegetable intake, and the dietary quality of their young children.To assess how the intervention influences weekly store sales of fruit and vegetables.To conduct an economic evaluation from individual, retailer and societal perspectives.To conduct a detailed process evaluation to examine: (1) intervention implementation in each store and the exposure and reach to participants, (2) mechanisms of intervention impact by exploring the experiences of participants and staff, and (3) how contextual factors, such as social influences, spatial access to supermarkets and government policy, influence intervention effects.

## Methods and analyses

### Study design

The (Women’s Responses to Adjusted Product Placement and its Effects on Diet (WRAPPED) study is a natural experiment with prospective matched controlled cluster design. It has a 6-month intervention period and baseline, 0–3 months post and 3–6 months follow-up assessments of intervention effects (figure 1).

**Figure 1 F1:**
[figure not shown]
Flow chart for the Women’s Responses to Adjusted Product Placement and its Effects on Diet study. F&V, fruit and vegetables.

### Study setting

WRAPPED focuses on women from disadvantaged backgrounds and will, therefore, sample from customer who shop at stores of the collaborating discount supermarket chain situated in more socioeconomically deprived neighbourhoods across England. The collaborating supermarket has over 900 stores nationwide and holds approximately 2% of the grocery market share in the UK.^23^

This study will sample 36 stores, 18 intervention and 18 control stores; allocation to intervention condition will be at the store level. Intervention stores will be selected, in a phased approach, from the collaborating supermarket’s ongoing refurbishment programme. Randomised controlled trial methodology in real-world supermarket research is limited because it requires commitment that is problematic in this highly competitive, commercial setting. In WRAPPED, randomisation of stores is also not viable within the company’s business model. Consequently, control stores will be matched to an intervention store based on: (1) sales profile, (2) customer profile and (3) neighbourhood deprivation (Index of Multiple Deprivation).^24^Matching on these factors increases the similarity of intervention and control stores and reduces effects of confounding. We will seek to select control stores located at least 20 miles from an intervention store to reduce contamination effects of control women shopping at intervention stores.

### Intervention and control conditions

The WRAPPED intervention incorporates both placement interventions from the typology of interventions in proximal physical micro-environments: availability and position.^25^ The intervention creates a healthier store layout by expanding the produce section to increase the availability of fresh fruit and vegetables, and positioning the section towards the front of the store. The supermarket chain will implement the intervention and will cover new display infrastructure and staff training costs (quality management, etc). The intervention will be implemented throughout the year, excluding the Christmas retail period, phased across 22 months and commencing in 2019. The logic model (figure 2) specifies the intervention components and the route of impact for the short term, medium term and long term. The model specifies that disadvantaged women will be exposed to the in-store product placement changes which will increase their purchasing of fresh fruit and vegetables (short-term outcome) that in turn will improve their own and their young children’s dietary quality (medium-term outcomes) and subsequently reduce inequalities in diet and obesity (long-term outcomes). This study will assess the short-term and medium-term outcomes.

